## Study aim

The aim of this paper is to report the study protocol used in an RCT examining the efficacy of a commercially available online weight loss program on initial weight loss and maintenance of lost weight up to 18 months.

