#### Phase 1 - Weight-loss interventions

Participants were initially randomized to one of three groups:

(1) Group 1, wait-list control; subsequently re-randomized to Group 2 or 3 after an initial 12-week control period;

(2) Group 2 followed the standard (Basic) commercial online weight loss program;

(3) Group 3 followed an extra support (Enhanced) version of the online weight loss program and received system-generated personalized feedback, based on diary entries and website use.

At the end of the initial 12 weeks of weight loss, those in Groups 2 and 3 could choose to undertake a further 12 weeks of weight loss or if they had achieved their goal weight, which was a loss of a minimum of 10% of initial body weight, they were re-randomized to one of two maintenance of lost weight programs (Phase 2).

#### Phase 2

Maintenance Group 1 (M1) was usual care whereas Maintenance Group 2 (M2) was enhanced support. Phase 2 will run for 12 months for those commencing after 6 months of weight loss or for 15 months for those entering after only 12 weeks of weight loss.

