### Randomization

Once written consent was obtained and baseline assessments completed participants were randomly allocated to one of the three Phase 1 groups (Figure 1) using a stratified randomized block design. Participants were stratified by gender and category of body mass index (25 to <30; ≥30 to <35 or ≥35 to 40) using blocks of variable length (either 3 or 6). Subjects received the next envelope in the sequence based on their stratified BMI and gender group. Envelopes were prepared ahead of time, sealed and distributed by a researcher not involved in data collection. Subjects were asked to not open their allocation envelope until they returned home. Subjects were re-randomized in the same way at the end of the weight loss phase to one of the two maintenance arms.

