#### Group M2 Enhanced maintenance of lost weight program

• All of the M1 program plus the following:

• Initial "welcome to weight maintenance phase" phone call from a trained consultant.

• Weekly and monthly system-generated, personalized reports summarizing energy balance and weight loss progress, website activity, and achievement of nutrition and physical activity targets.

• Regular questionnaires to help the user identify and prioritize behaviors (diet, physical activity and lifestyle-related) that can help achieve weight maintenance and prevent rebounds.

• Continuation of email, text and phone reminders to self-monitor weight, diet and physical activity, adjusted for maintenance time frame.

• Specific "relapse" weight loss program if weight rebounds by more than 3% of their baseline weight, including an initial phone call from a trained consultant.

• Congratulation emails for successful maintenance of lost weight.

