### Data analysis

Analysis will be on an intention-to-treat basis. Analysis of covariance will be used to test for differences in weight loss between groups at 3 months. The model will be fitted using linear regression with weight at 3 months as the outcome variable, treatment group as the predictor variable of interest and weight at baseline included as a covariate. Other independent variables included in the model will be: gender, kilojoule intake at baseline and physical activity at baseline. Differences in weight loss between groups in the weight maintenance phase will be analysed using generalised linear mixed models (GLMM). The outcome in the model will be the individual's weight at the post treatment assessments, the main predictor of interest will be treatment group and baseline weight will be included as a covariate. Other independent variables included in the model will be: time, gender, kilojoule intake at baseline and physical activity at baseline.

Statistical significance of the primary efficacy analysis (at three months and 18 months) will be based on Hochberg's multiple testing procedure with the family wise error rate for each time point held at 2.5%. All secondary hypothesis tests will be performed using a 2-sided 5% significance level. In addition, linear regression and GLMM will be used to describe relationships among the various dependent and independent variables.

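### The maintenance model leaves out the Phase 1 programme (Basic or Enhanced) and the entry route, which costs some precision and averages two different M2–M1 contrasts, without biasing the comparison

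*Protocol article*

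**What the plan says.** The Design section describes two successive randomisations. In Phase 1 people follow Basic or Enhanced. Wait-list participants join one of these later: "Group 1, wait-list control; subsequently re-randomized to Group 2 or 3 after an initial 12-week control period". People then enter M1 or M2, either after 12 weeks if they have reached their weight goal or after 24 weeks. Phase 2 lasts 15 months for the first route and 12 months for the second.

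For the first allocation, the Randomization section says "Participants were stratified by gender and category of body mass index (25 to <30; ≥30 to <35 or ≥35 to 40) using blocks of variable" size. For maintenance it says "Subjects were re-randomized in the same way at the end of the weight loss phase to one of the two maintenance arms". Phase 1 programme is not named as a stratum.

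For the maintenance model, the Data analysis section takes weight at the post-treatment assessments as the outcome and says "the main predictor of interest will be treatment group and baseline weight will be included as a covariate". It then adds: "Other independent variables included in the model will be: time, gender, kilojoule intake at baseline and physical activity at baseline". The section ends with a general statement that "linear regression and GLMM will be used to describe relationships among the various dependent and independent variables", which names neither Phase 1 programme nor carry-over.

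The description of M2 includes "Continuation of email, text and phone reminders to self-monitor weight, diet and physical activity, adjusted for maintenance time frame".

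**The concern.** Phase 1 programme is a randomised factor that may still affect weight at 18 months, and it is known for everyone before maintenance allocation. A model that lists its terms and omits this one leaves any lasting Basic–Enhanced difference in the residual.

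The same holds for entry route. Those entering at 12 weeks have by definition lost at least 10% of initial weight. Their 6-month visit falls about three months into maintenance, whereas for 24-week entrants it falls at maintenance entry. No listed term reflects this.

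Origin also changes what M2–M1 means. Personalised weekly feedback and escalating email, text and phone reminders are extras of Enhanced in Phase 1. M2 carries on reminders and personalised reports for former Enhanced users and introduces them for former Basic users. M1 is a partial step down for the first group and roughly level, with some added prompts, for the second. A single coefficient cannot separate a benefit of adding support from a harm of reducing it.

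**Working it through.** **Inputs.** From the Sample size section: difference 1.5 kg/m², SD 1.5, two-sided 0.05, power 90%, 48 per maintenance group (24 men and 24 women). Assumed, because the article gives no figure: half of each maintenance group comes from each Phase 1 programme, and a Basic–Enhanced difference d of 0.5, 1.0 or 1.5 kg/m² persists to 18 months. The top value is the plan's own target difference, used as an upper case. The scale is BMI because the sample size is stated in BMI; the model itself is written for weight.

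**1. The plan's own figure.** n = 2(1.96 + 1.28)²(1.5/1.5)² ≈ 21.0, so 22 per group (23 with the t distribution). The stated 24 per sex per group is close to this, so 48 reproduces as 2 × 24 if the calculation was made within each sex. A single pooled comparison would need only 22 to 23 per group.

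**2. Precision lost.** With within-arm SD 1.5 and an even split, leaving the programme term out gives residual variance 2.25 + 0.25d².

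| d (kg/m²) | Residual SD without term | Removable variance | SE reduction from adding term |
|---|---|---|---|
| 0.5 | 1.521 | 2.7% | 1.4% |
| 1.0 | 1.581 | 10% | 5.1% |
| 1.5 | 1.677 | 20% | 10.6% |

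The last column is 1 − 1.5/(residual SD). Taken the other way, the SE without the term is 1.4%, 5.4% or 11.8% larger than with it. If the stated SD of 1.5 already contains the Phase 1 difference, the SD with the term is 1.48, 1.41 or 1.30, and the reduction is 1.4%, 5.7% or 13.4%.

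**3. Chance imbalance is the same cost.** With 48 of 96 people from Enhanced and 48 per arm, the M2–M1 difference in the share from Enhanced has SD 10.3 percentage points (95% about ±20). The resulting shift in the estimate has SD 0.05, 0.10 or 0.15 kg/m². At d = 1.5, combining it with the within-arm SE of 1.5√(2/48) = 0.306 gives √(0.306² + 0.154²) ≈ 0.343. The residual SD in the table gives 1.677√(2/48) ≈ 0.342. The shift is already inside the wider SE and must not be added to it.

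**4. Power for 1.5 kg/m².** At 48 per group and 0.05, power without the term stays above 99% for all three values of d. At d = 1.5 and 0.025, 1.5/0.342 − 2.24 = 2.14, or about 98%. At 24 per group (within one sex, 0.05) it is 92.7%, 90.8% or 87.3%, against 93.4% when d = 0.

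**5. Interaction.** With 24 per cell the SE is 1.5√(4/24) = 0.612. For an interaction of 1.5 kg/m², 1.5/0.612 − 1.96 = 0.49, or about 69% power.

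**The case against.** The strongest reply is that M1 and M2 are assigned by a new randomisation, so origin is balanced in expectation and M2–M1 is valid without a Phase 1 term. That stands. A reader might infer that carry-over biases the maintenance result, and the documents do not support it. A reader might also take the 95% imbalance of 20 points times 1.5 kg/m², or 0.30 kg/m², as a likely error. That joins an extreme imbalance to full persistence of the largest assumed difference, is still below one standard error (0.34), and is already counted in it.

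Baseline is not defined for the maintenance model. If it means maintenance entry, baseline weight absorbs part of any Phase 1 difference and the precision loss is smaller. This stands as a limit on the figures.

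M1 is not a full withdrawal of support. Its description keeps weekly email and text prompts and feedback on weigh-ins, so the step down for former Enhanced users is partial.

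A reader might further infer that Basic and Enhanced are never compared after 3 months, although the aim covers "efficacy of a commercially available online weight loss program on initial weight loss and maintenance of lost weight up to 18 months". That is not shown. Treatment group is undefined in the maintenance model, and using Hochberg's procedure at 18 months suggests more than one comparison there.

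Finally, the average M2–M1 effect over all entrants is a legitimate target, and secondary subgroup analyses are often left to an analysis plan. That is a reason to keep the interaction secondary. It does not answer the covariate point, because the article sets out the model's terms explicitly.

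**Conclusion.** The point holds as a matter of efficiency and interpretation. The stated maintenance model omits Phase 1 programme and entry route, and the named strata do not include Phase 1 programme. The M2–M1 estimate is unbiased and overall power at 48 per group stays at about 98% or more. The price is a standard error that the programme term could reduce by about 1.4%, 5% or 11% if 0.5, 1.0 or 1.5 kg/m² persisted. These persisting differences are assumptions, with 1.5 as the within-arm SD, an even split by origin and nothing absorbed by baseline weight. No figure is offered for entry route, since the article does not say how many people take each route.

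The second cost does not depend on those assumptions: support continues for some M2 entrants and is new for others, and no stated analysis looks at this.

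**What to change.** Add Phase 1 programme (Basic or Enhanced, with former wait-list participants coded by the programme they were re-randomised to) and entry route (12 or 24 weeks) as fixed covariates in the maintenance model. Both are known before maintenance allocation, so neither can be affected by M1 or M2. State which weight is meant by baseline in that model. Report M2–M1 separately for former Basic and former Enhanced users, with the programme-by-maintenance interaction as a labelled secondary estimate.

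The cost is one or two degrees of freedom and a few lines of text; the data are already held. The interaction will be imprecise (about 69% power even for 1.5 kg/m²), so a null result should not be read as showing no difference. Stratifying the re-randomisation by Phase 1 programme is probably no longer possible, since the article reports that step in the past tense. The analysis is still written as planned, so the model can be changed before results are seen.

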### Sample size

Based on having 90% power to detect a significant difference in BMI between weight loss groups of 1.5 kg/m^2^, assuming the SD of BMI is 1.5 and using a two-sided significance level of 0.05, a sample size of 48 participants (24 males and 24 females) is needed for each maintenance group at 18 months. This sample size is within the range of other web-based weight loss intervention studies [13].

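### The stated 90% power is calculated at two-sided 5%, but the primary 18-month test is judged within 2.5%, so the figure does not describe the planned test

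*Protocol article*

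**What the plan says.** The Sample size section gives one calculation. Its target is stated as "Based on having 90% power to detect a significant difference in BMI between weight loss groups of 1.5 kg/m^2", with the variability given as "assuming the SD of BMI is 1.5" and the test carried out "using a two-sided significance level of 0.05". The result is "a sample size of 48 participants (24 males and 24 females) is needed for each maintenance group at 18 months". The section mentions neither a division of alpha over time points nor a multiple-testing procedure.

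The Data analysis section names 3 and 18 months as the two primary time points and applies Hochberg's procedure "with the family wise error rate for each time point held at 2.5" per cent. It does not say whether this 2.5% is one-sided or two-sided, and it does not list the tests in each family. The sentence that follows sets secondary tests at a two-sided 5% level. The models pool men and women, with gender as a covariate. No separate primary test by sex is described.

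**The concern.** The level used for sizing is the one the plan assigns to secondary tests, not the one it assigns to the primary analysis. The 18-month maintenance comparison is both the comparison that was sized and one of the two primary time points, so the two sections speak about the same test and give it different levels. Nothing in the article reconciles them.

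A power figure is used when a null primary result is interpreted. If it was worked out for a more lenient test than the one performed, that interpretation starts from the wrong number. The error could matter or be trivial, depending on which comparison the 90% describes, and the article leaves that open too.

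**Working it through.** **Inputs (Sample size section).** Difference d = 1.5 kg/m², SD s = 1.5, so d/s = 1. Power 90%, two-sided alpha 0.05, 48 per maintenance group, of whom 24 are of each sex.

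**Inputs (Data analysis section).** 2.5% at 18 months.

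**Assumptions.** The 2.5% is two-sided. There are two maintenance arms and one outcome, hence one contrast at 18 months, for which Hochberg's threshold is the full 0.025. Allocation is equal.

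**Step 1: reproduce the stated size.** The normal formula is n per arm = 2(z₁₋α/₂ + z₀.₉₀)² / (d/s)².

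- At alpha 0.05: 2(1.960 + 1.282)² = 21.0, so 22 per arm. The noncentral t calculation gives 23.
- Done within each sex and doubled, this is 2 × 23 = 46 per group, close to the stated 48 (24 + 24).
- It does not reproduce 48 as a pooled group size, because 48 per group gives 99.8% power at this level (Step 3).

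So 48 is best explained by a calculation within each sex. The article does not say this. It is inferred from the 24 + 24 split.

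**Step 2: size needed at two-sided 0.025.**

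- Normal: 2(2.241 + 1.282)² = 24.8, so 25 per arm. Noncentral t: 27.
- By sex, that is 2 × 25 = 50 or 2 × 27 = 54 per maintenance group, against 48 stated.

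**Step 3: power at the stated size.** The normal approximation is Φ(√(n/2) · d/s − z₁₋α/₂).

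- n = 24: √12 = 3.464. At 0.05, Φ(3.464 − 1.960) = 93.4%. At 0.025, Φ(3.464 − 2.241) = 88.9%.
- n = 48: √24 = 4.899. At 0.05, Φ(4.899 − 1.960) = 99.8%. At 0.025, Φ(4.899 − 2.241) = 99.6%.

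| Reading | Method | Two-sided 0.05 | Two-sided 0.025 |
|---|---|---|---|
| 24 v 24, within sex | normal | 93.4% | 88.9% |
| 24 v 24, within sex | noncentral t | 92.4% | 87.0% |
| 48 v 48, pooled | normal | 99.8% | 99.6% |
| 48 v 48, pooled | noncentral t | 99.8% | 99.5% |

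By the t calculation the change of level costs 92.4 − 87.0 = 5.4 points within sex and 99.8 − 99.5 = 0.3 points pooled.

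**Step 4: sidedness.** A one-sided 2.5% test has critical value 1.960, the same as a two-sided 5% test. On that reading the two sections agree for a single contrast.

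**The case against.** The strongest reply is that the planned test loses almost nothing. The analysis pools the sexes, and with the stated SD and 48 per group its power stays at 99.5%. On that reading 90% understates the power, and mainly because it is a by-sex figure, not because of the alpha. This stands. It limits the consequence but does not remove the inconsistency, since 90% is then still not the power of the planned test.

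A second reply is that the 2.5% may be one-sided. The text does not exclude this. However, 2.5% at each of two time points adds up to 5%, and the next sentence uses a two-sided 5% for secondary tests, so a two-sided split is the more natural reading.

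Three stronger readings are tempting, and the document does not support them.

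- **That the trial is underpowered.** Power falls below 90% only for 24 v 24 within sex, and no primary test of that kind is described. One could also back-solve the SD at which 48 v 48 gives exactly 90% (about 2.24) and show a loss from there, but the article states 1.5.
- **That the 3-month power is short by a stated amount.** Three groups are randomised in Phase 1, so three pairwise tests are possible. The article gives no 3-month group size, claims no 3-month power and does not list the tests in the family.
- **That 0.025/3 = 0.0083 is the operative 3-month level.** It is only Hochberg's strictest threshold. The procedure is step-up, so power at that threshold alone is a lower bound. If 24 per arm and three tests are assumed, simulation of the whole procedure gives about 80% to 82% per true comparison when one group differs by 1.5. It gives about 87% to 89% for adjacent groups when all three are 1.5 apart. The lower figure of each pair uses t-tests, the higher normal tests. With 48 per arm every such figure is 99% or more.

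**Conclusion.** The point holds as an inconsistency in a planning figure: the 90% was computed at a level that the plan does not use for its primary test at 18 months. Its size depends on what the 90% describes: 87.0% in place of 92.4% if it is a by-sex figure, 99.5% in place of 99.8% if the sexes are pooled as in the analysis model. The pooled primary comparison is not shown to lack power.

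This rests on a two-sided 2.5%, a single 18-month contrast, equal arms and the stated SD of 1.5. The figures are for BMI, as in the Sample size section. The models in the Data analysis section use weight, so none of them is exactly the power of the fitted model.

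**What to change.** Keep the sample size. In the Sample size section, recompute and restate the power of the 18-month M1 v M2 comparison at the 2.5% level. Say whether that level is one-sided or two-sided, and whether the figure applies within each sex or to the sexes pooled. If the two-sided reading is confirmed, the values are those in the 0.025 column of the table.

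If power at 3 months is also to be reported, give it for the complete Hochberg step-up procedure, with the actual 3-month group sizes and a list of the tests in the family.

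The cost is a few sentences and a short recalculation. No participants are added and the design does not change. A by-sex figure would be slightly less favourable than the one now printed, and a pooled figure more favourable.

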## Discussion

The study described in this paper is one of the first randomized controlled trials of its kind in Australia. The results of this study of a commercially available program will provide much needed information about the efficacy of treatment approaches using the internet in real world settings. It is important internationally because web-based weight management interventions for adults to date have only shown moderate success and commercially available online programs have not been tested for efficacy using a robust study design [13].

This RCT addresses some of the short-falls in current web-based weight management interventions by (i) incorporating a large sample size compromised of representative samples of both men and women, and an intention to treat analysis plan; (ii) having an 18-month follow-up period, thereby allowing assessment of medium term program effectiveness; (iii) including several important secondary outcomes (metabolic profile, self-monitoring of dietary intake and physical activity, quality of life), and (iv) inclusion of a maintenance of lost weight phase. Data demonstrating whether the study yields positive long-term results from the end of the maintenance phase or not will allow other research groups to benefit from our experience and facilitate the implementation of well-designed RCTs to address the lack of quality web-based interventions. Importantly it will also ascertain whether commercial providers can deliver efficacious web-based programs targeting this important public health issue.

